### Sensitivity Analysis

A sensitivity analysis will be implemented to propagate the uncertainty of the estimations to the model's results. We will use a multivariate and stochastic sensitivity analysis performed by 5,000 Monte Carlo simulations. The cost-effectiveness plane will represent all pairs of solutions of the model.

The results of the one-way sensitivity analysis will be reported in the tornado diagram, which depicts graphically how variations in each input affect the outcome. In addition, the 95% CI intervals around the base case values will be derived using the 2.5 and 97.5 percentiles calculated from the sensitivity analysis.

The tornado diagram will be stacked in order of decreasing width, indicating that variations in inputs near the top (Total Costs of Robotics procedures) have the most significant effect on the outcome, while variations in inputs near the bottom (QALYs discount rate) have relatively small effects on the outcome.

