## Aims of the Study

### Primary Aim of the Study

To determine if robotic surgery is more cost-effective than laparoscopic surgery in several surgical conditions and patient populations. The present prospective study will evaluate the incremental cost per quality-adjusted life year (QALY) gained from healthcare perspectives.

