### Cost-Effectiveness Analysis

The economic evaluation will be performed as cost effectiveness and cost–utility analyses from a healthcare perspective, with a time horizon of 3 months.

The cost–utility endpoint will be the cost per QALY. The results will be reported in accordance with CHEERS guidelines (23). Data will be collected in the early post-operative period of time (3 months from the surgery) in order to capture as much as possible only the QoL mainly related to the surgical approach instead of the issues related to all treatment process (adjuvant treatment, stoma issues, etc.) which patients are dealing with in a later period of time.

An independent company (Institute for Validation of Clinical Efficacy - IVEC) will perform the financial analysis, eliminating the risk of an observer bias.

A model-based cost-utility analysis estimating mean costs and QALYs per patient will be performed. A stochastic cost-utility analysis will be undertaken. The incremental cost-effectiveness ratio (ICER) will be estimated using the overall costs of the robotic and laparoscopic procedures and QALYs derived from patient interviews to find the incremental cost per QALYs gained.

The INB will be calculated to estimate decision-makers maximum willingness to pay (WTP) for a QALY gained. The INB will be calculated as the mean QALYs per patient multiplied by WTP threshold minus the mean cost per patient for the treatment. The decision rule is to adopt the treatment if the INB > 0, and the alternative with the highest INB represents best value for money.

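### The percentile interval rule does not exclude the ICER, whose percentiles cannot be interpreted if the simulated QALY differences straddle zero

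*Protocol article*

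**What the plan says.** The Primary Aim says the study "will evaluate the incremental cost per quality-adjusted life year (QALY) gained from healthcare perspectives". The Cost-Effectiveness Analysis section repeats this ("The cost–utility endpoint will be the cost per QALY"), works "with a time horizon of 3 months", and estimates an ICER from overall costs and QALYs "to find the incremental cost per QALYs gained". The same section also plans the INB, with adoption if it exceeds zero.

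The Sensitivity Analysis section describes a multivariate stochastic analysis "performed by 5,000 Monte Carlo simulations" and a cost-effectiveness plane showing every simulated pair. It then states one interval rule: 95% intervals around the base case values, "derived using the 2.5 and 97.5 percentiles calculated from the sensitivity analysis". It does not list those values, leave out the ICER, or say what happens when a simulated QALY difference is zero or negative. The Acceptability Curve section adds a curve over willingness to pay, with thresholds of 20,000 and 30,000 euro per QALY.

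**The concern.** The ICER is a ratio, and its values have no consistent ordering once the denominator can change sign. A negative ICER arises when robotic surgery is cheaper and better, and also when it is costlier and worse. A positive ICER arises when it is costlier and better, and also when it is cheaper and worse. Sorting the simulated ratios and cutting at 2.5% and 97.5% then puts opposite conclusions at the same end of the list.

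The interval rule is general and the ICER is the declared cost-utility endpoint, so an analyst following the text could reasonably apply the rule to it. At stake is whether the interval printed beside the headline ratio can be read at all.

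**Working it through.** **Inputs from the article.** Horizon 3 months, so at most 0.25 QALY per patient at full health. Minimum 30 per arm in each procedure comparison, with 5% loss assumed: 30 × 0.95 = 28.5, taken as 28 evaluable. Thresholds 20,000 and 30,000 euro per QALY. The article gives no expected QALY or cost difference and no SD, so there is no planned figure to reproduce.

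**Assumptions, not from the article.** SD of the 3-month QALY 0.02 to 0.05; normal, uncorrelated differences (robotic minus laparoscopic); costs as listed below.

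**Step 1: when do simulated QALY differences straddle zero?** SE = SD × √(2/n), and the share of draws below zero is Φ(−ΔQ/SE). That share is under 2.5% only if ΔQ exceeds 1.96 × SE. Dividing by 0.25 gives the utility gap that must last the whole 3 months. With n = 28 per arm:

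| QALY SD | SE | ΔQ needed | Sustained utility gap |
|---|---|---|---|
| 0.02 | 0.0053 | 0.0105 | 0.042 |
| 0.03 | 0.0080 | 0.0157 | 0.063 |
| 0.04 | 0.0107 | 0.0210 | 0.084 |
| 0.05 | 0.0134 | 0.0262 | 0.105 |

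With 30 per arm the needed gain is 0.0101 to 0.0253.

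**Step 2: what the percentile rule then gives.** 30 per arm, extra cost 1,500 euro, cost SD 4,000 euro (SE 4,000 × √(2/30) = 1,033); 1,000,000 draws:

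| QALY gain | QALY SD | Draws with ΔQ < 0 | ICER point | ICER 2.5% to 97.5% (euro/QALY) |
|---|---|---|---|---|
| 0.005 | 0.04 | 31% | 300,000 | −2.1 to +2.2 million |
| 0.0125 | 0.03 | 5% | 120,000 | −0.63 to +1.07 million |
| 0.02 | 0.03 | 0.5% | 75,000 | about −33,000 to 344,000 |
| 0.03 | 0.03 | 0.01% | 50,000 | about −18,000 to 153,000 |

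In the first row, 5% of draws are cheaper and better and 29% are costlier and worse; both have a negative ICER. The extreme negative limit comes from costlier-and-worse draws with a QALY difference just below zero, which are ranked as if they were the most favourable. In the last two rows almost every denominator is positive. The negative lower limit then simply reflects cheaper-and-better draws, and the interval can be read.

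**Step 3: other inputs.** 28 per arm, extra cost 2,000 euro, cost SD 3,000 euro, 5,000 draws. At QALY SD 0.03 the ICER interval is about −3.3 to +3.3 million at a gain of 0.005 (27% of draws negative), −1.7 to +1.9 million at 0.01 (11%), and 12,000 to 425,000 at 0.02 (under 1%). At a gain of 0.02 with SD 0.05, about 7% are negative and the interval is about −0.55 to +0.93 million.

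**Step 4: the INB on the first case of Step 2.** INB at 20,000 = 20,000 × 0.005 − 1,500 = −1,400. QALY SE = 0.04 × √(2/30) = 0.01033. SE of INB = √((20,000 × 0.01033)² + 1,033²) ≈ 1,053. 95% interval: −1,400 ± 1.96 × 1,053, about −3,464 to 664 euro. This is finite, ordered and readable.

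**Step 5: coverage.** Repeated simulated trials gave the ICER percentile interval about 95% to 96% coverage in the first case of Step 2 and about 97% in the second. At gains of 0.001 to 0.002 (SD 0.03 to 0.04) coverage fell to about 55% to 90%.

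**The case against.** The strongest reply is that the sentence never names the ICER. It speaks of base case values in the plural and stands beside the tornado diagram; for mean costs, mean QALYs and the INB a percentile interval is sound. That is right: a reader might infer that the article explicitly prescribes an ICER percentile interval, and it does not. But the rule is stated without exception and the ICER is the declared endpoint, so this is a stated rule drawn too broadly. It is more than a detail left to a fuller document.

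Three further readings are tempting and also go too far.

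- That zero crossing is certain. The article gives no QALY difference or SD, 30 per arm is a minimum, and crossing is negligible at gains of about 0.02 to 0.03 QALY with a modest SD.
- That the interval lacks 95% coverage. Step 5 shows roughly nominal coverage in both cases where the interval cannot be read, with clear failure only at very small gains. The defect is in interpretation.
- That readers could not judge cost-effectiveness. The adoption rule uses the INB, the plane shows the quadrants, and the acceptability curve gives the probability at each willingness to pay. None of these depends on an ICER interval.

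These points narrow the concern. They do not make an ICER percentile interval readable when the denominator changes sign.

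**Conclusion.** The point holds in a limited form. The percentile rule covers base case values without excluding the ICER, and for small QALY gains it would give the primary ratio an interval that cannot be interpreted. Under the assumed QALY SD of 0.02 to 0.05 and 28 to 30 per arm, this is likely unless the gain reaches about 0.01 to 0.026 QALY, a utility gap of about 0.04 to 0.10 held for the full 3 months. Above that range the interval is usable. The thresholds rest on assumed SDs and normality, the interval limits also on assumed costs and zero correlation; larger groups would lower the thresholds (four times the number per arm halves them). The INB decision rule, the plane and the acceptability curve are unaffected. The change should be made, but it does not undermine the planned decision analysis.

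**What to change.** In the Sensitivity Analysis section, name the quantities that receive 2.5/97.5 percentile intervals: incremental cost, incremental QALY, and INB at 20,000 and 30,000 euro per QALY. Report the ICER as a point estimate with the share of simulations in each quadrant of the plane. Give an ICER interval, for example Fieller's, only when the 95% interval for the QALY difference excludes zero. Renaming the INB as the primary summary is not needed.

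The cost is one paragraph of wording. The 5,000 simulations already planned supply everything and no new data are required. The downside is that there will often be no interval on the ICER itself.

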### Acceptability Curve

The analysis will also include a cost-effectiveness acceptability curve that plots the probability that the robotic technique is cost-effective relative to laparoscopy over a reasonable range of levels of WTP.

Although there is no specific willingness to pay threshold in healthcare in Spain, as described above, according to the National Institute for Health Care Excellence (NICE) (30) and the Spanish Recommendations on Economic Evaluation of Health Technologies (31) a WTP of 20,000 € and 30,000 € per QALY will be used as a threshold to recognize which treatment is most cost-effective.

## Methods for Minimizing Bias

The number of patients screened, the number included, and those analyzed will be reported, and differences will be explained. In addition, the patient flow and the Consolidated Standards of Reporting Trials (CONSORT) flowchart will be reported in the final analysis (32).

In addition, analysis will be stratified according to each surgeon's previous experience before starting the study, type of hospital (public, university) and total number of beds.

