## The Rationale for the Study

The current debate about introducing a new technology mainly concerns its cost-effectiveness (15). Only a cost-effectiveness analysis can shed light on uncertainties concerning the economic impact of robotic vs. laparoscopic surgery. However, reliable, prospective, adequately designed cost-effectiveness studies are still lacking (16–21).

QoL after a surgical procedure can be measured through different scores (22). In order to conduct cost-effectiveness studies, QoL needs to be objectively and consistently measured, using validated tools. The most used scores to grade QoL are the generic SF-36 and the EuroQol EQ-5D-5L tests, that can be transformed into QALYs, giving a more objective view of the patient's improvement after the planned treatment (health perspective) (23).

Apart from prospective series, some studies only used a decision-analytic model derived from available literature for costs, QoL and outcomes (24). However, these results must be interpreted with great caution since the insufficient data available in the literature imply a high risk of bias.

According to the pyramid of evidence, randomized clinical trials represent the highest level of study types. However, in a surgical setting of robotic vs. laparoscopic approach, these trials are difficult to be performed (e.g., expensive, ethical issue, blinding) and generalized (strict inclusion criteria) (25). Hence, prospective, adequately designed and conducted non-randomized clinical trials can provide very clinically relevant information.

A well-designed cost-effectiveness study would answer whether its superiority justifies the higher costs of robotics in terms of gained QoL after surgery. This protocol describes the study of nationwide assessment of the cost-effectiveness of the laparoscopic vs. robotic approach, which will define which approach is more convenient for each condition or patient.

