## Study Design

The Spanish national study on cost-effectiveness differences among robotic and laparoscopic surgery (ROBOCOSTES) is designed as a prospective, multicentre, national, observational study conducted in Spain between the 15th of January and the 15th of December 2022.

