### Study Population

Patients are considered eligible to enter the study if they meet the following inclusion criteria:

1. Adults aged ≥18 years of age.

2. Consecutive patients undergoing: distal pancreatectomy, gastrectomy (total and subtotal), sleeve gastrectomy, inguinal hernioplasty with mesh, rectal resection for cancer, Heller cardiomiotomy and Nissen procedure.

3. Type of disease approachable by both laparoscopic and robotic minimal access surgery.

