### Exclusion Criteria

The following exclusion criteria will apply:

Patients with peritoneal metastases.Patients with ASA physical status IV-V.Emergency surgery: that is required to deal with an acute threat to life.Inability to give written informed consent.Surgery for recurrent disease of the included procedure.Palliative surgery: performed only for symptom relief even despite negligible impact on the patient's survival.

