## Data Completeness

### Questionnaires

All participants will be asked to provide an additional informed consent to receive the validated QoL questionnaires EuroQol EQ-5D-5LTM (official Spanish version) and will be asked to score five aspects of health status using the EQ-5D™ questionnaire: mobility, self-care, usual activities, pain/complaints, and mood (anxiety/depression). This questionnaire is considered the most representative QoL tool for cost-effectiveness studies (28). Patients will receive questionnaires at inclusion, one, and 3 months after surgery, by mail, digitally, or in person, according to their preference.

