## Sample Size Calculation and Statistical Methods

### Sample Size

There are concerns about calculating power and sample size in cost-effectiveness studies (28). Although there is some uncertainty, the Incremental Net Benefit (INB) is a measure that is easier to interpret and work with, since a positive INB means that the new proposed treatment is cost-effective (29). Medicare calculations of power and sample size are calculated against some value of Maximum Willingness to Pay (WTP) for a unit of treatment effect. The WTP is defined from a societal perspective, and, although in Spain there is no specific WTP threshold in healthcare, according to the National Institute for Health Care Excellence (NICE) (30) and Spanish Recommendations on Economic Evaluation of Health Technologies (31) we use a WTP of 20,000 € and 30,000 € per QALY as a threshold, to recognize which treatment is most cost-effective, as follow:

$$\begin{array}{l} \text{INB}=\left[\left(\text{EffectNew-EffectComparatore}\right)*\text{WTP}\right]\\ -\left(\text{CostNew-CostComparator}\right) \end{array}$$

This sample size calculation was realized with consultation of two statisticians.

Considering previous retrospective reports on cost-effectiveness studies (16–21) in which a minimum of 3,000 € for QALY gained was considered cost-effective, assuming a 5% lost-to-follow-up-rate and the two-sided significance level (α) set at 5% and power (1-β) at 80%, a minimum total of 60 patients need to be allocated in each procedure group comparison (30 laparoscopic vs. 30 robotic).

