### Statistical Method

Data will be analyzed using the SPSS statistical program (SPSS Inc. Chicago, IL, USA). In order to compare the means of the quantitative variables when these followed a normal distribution, a variance analysis and Student's *t-*test will be used. For the rest of the variables, both the Mann-Whitney and Kruskal-Wallis tests will be performed. For categorical variables, a Chi-square test will be implemented. Results with a *P*-value lower than 0.05 will be considered statistically significant.

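### In this non-randomised comparison, neither the stated analysis nor the stated bias-control measures adjust for patient factors or baseline quality of life

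*Protocol article*

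**What the plan says.** Study Design says that the study "is designed as a prospective, multicentre, national, observational study conducted in Spain". The Rationale for the Study defends this choice on the ground that "prospective, adequately designed and conducted non-randomized clinical trials can provide very clinically relevant information". No allocation rule is given.

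Three parts of the protocol article then describe how the arms are compared.

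- **Statistical Method** names ANOVA and Student's t-test ("In order to compare the means of the quantitative variables when these followed a normal distribution"), Mann-Whitney and Kruskal-Wallis tests otherwise, and chi-square for categorical variables.
- **Cost-Effectiveness Analysis** announces a model-based, stochastic cost-utility analysis. The ICER comes from overall costs and QALYs, and the INB from mean QALYs times the willingness-to-pay threshold minus mean cost. The decision rule is to adopt if INB exceeds zero.
- **Methods for Minimizing Bias** lists patient-flow reporting and stratification by surgeon experience, "type of hospital (public, university) and total number of beds".

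On the data available, Questionnaires states: "Patients will receive questionnaires at inclusion, one, and 3 months after surgery". Sample Size requires "a minimum total of 60 patients need to be allocated in each procedure group comparison (30 laparoscopic vs. 30 robotic").

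**The concern.** Without randomisation, the two arms of each procedure can differ in who is operated on as well as in how. The article has a place for the tests, a place for the economic estimator and a place for bias control. It fills all three without naming a patient characteristic or baseline utility. Surgeon experience, hospital type and bed count describe the setting; stratifying on them does not balance the patients.

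If the article is followed as written, differences in case mix and in pre-operative EQ-5D are reported as effects of the robot on cost, QALYs and INB. Because the adoption rule depends on the sign of the INB, a bias of a few hundred euros can reverse the decision whenever the true INB is smaller than the bias and of opposite sign. A larger sample does not remove such a bias.

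**Working it through.** **1. What is controlled, and by what.**

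| Source of difference | Handled in the article by |
|---|---|
| Procedure | Comparison within procedure (Sample Size) |
| Feasibility of either route | Eligibility: "Type of disease approachable by both laparoscopic and robotic minimal access surgery" |
| Very high operative risk | Exclusion: "Patients with ASA physical status IV-V" |
| Emergency, recurrent, palliative, peritoneal metastases | Exclusion Criteria |
| Surgeon experience, hospital type, beds | Stratification |
| Age, ASA I to III, indication or subtype | Nothing stated |
| Baseline EQ-5D | Collected, no stated use for adjustment |

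The Sensitivity Analysis section uses the word multivariate, but it describes 5,000 Monte Carlo draws that propagate input uncertainty. That widens or narrows the interval around the estimate and does not remove confounding.

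**2. The plan's own figure, for scale.** The 30 per arm cannot be reproduced, because no standard deviation is given. Assume that EUR 3,000 is a difference in INB (the article words it per QALY gained). With two-sided 5% and 80% power, n per arm = 2 × (1.960 + 0.842)² × SD² / 3,000².

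- SD 3,000: 16, which becomes 17 after dividing by 0.95.
- SD 4,000: 28, which becomes 30.
- SD 5,000: 44, which becomes 47.

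So 30 per arm matches an SD near EUR 4,000. At 30 × 0.95 = 28.5 evaluable per arm, the back-solved SD is 4,042 and SE = 4,042 × √(2/28.5) ≈ EUR 1,071.

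**3. How a baseline utility gap reaches the INB.** With EQ-5D at 0, 1 and 3 months and trapezoid areas (assumed), the weights in years are 1/24, 1/24 + 1/12 = 1/8, and 1/12, which sum to 0.25. The gap sizes below are assumptions; the thresholds are the article's.

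| Gap | Acts through | QALY | INB at EUR 20,000 | INB at EUR 30,000 |
|---|---|---|---|---|
| 0.05 | all three times | 0.05 × 0.25 = 0.0125 | 250 | 375 |
| 0.10 | all three times | 0.10 × 0.25 = 0.025 | 500 | 750 |
| 0.05 | baseline only | 0.05/24 = 0.0021 | about 42 | about 62 |
| 0.10 | baseline only | 0.10/24 = 0.0042 | about 83 | about 125 |

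**4. Effect on a 5% test.** With bias b, the rejection rate under no true difference is 1 − Φ(1.96 − b/SE) + Φ(−1.96 − b/SE). With SE 1,071:

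- b = 250: 5.6%
- b = 375: 6.4%
- b = 750: 10.8%
- b = 1,000: 15.4%

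An illustrative simulation (20,000 runs, 28 per arm) put a 0.5 SD imbalance in a patient factor correlated 0.5 with the outcome. The unadjusted test rejected in 15% of runs. This agrees with the formula, since the bias is 0.5 × 0.5 = 0.25 SD, or about 0.25 × 4,042 ≈ EUR 1,010.

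**5. Stratification at the minimum size.** If each of the three variables is split in two and all are crossed (assumptions), there are 8 cells of 60/8 = 7.5 patients, or 3.75 per arm. Taken one at a time with equal halves, each stratum has 15 per arm.

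**The case against.** The best reply is that this is an article. Covariate lists and weighting models usually sit in a full protocol or analysis plan, which is not shown. Statistical Method is a generic paragraph that never mentions QALYs or INB, and the economic model is not described. A reader might therefore infer too much in saying that the primary INB is fixed as an unadjusted t-test; the text does not say so. What remains is that the article does describe its estimator and has a section devoted to bias, and neither contains patient-level or baseline adjustment. That goes beyond leaving detail to another document.

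A second reply is that selection is already restricted by eligibility, consecutive inclusion and comparison within procedure. This stands in part: ASA, for example, is limited to I to III. It does not equalise the arms within those limits.

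Third, the sizes are modest. A persistent gap of 0.05 moves a 5% error rate only to about 6%, and the baseline weight alone gives tens of euros. This also stands for the utility part. Confounding of cost could be larger, but nothing in the document allows it to be sized.

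Three stronger readings are tempting and are not supported:

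- **Stratification cannot work.** The article does not say that the three variables are crossed or how many levels each has, and 60 is a minimum.
- **This is the main threat to the primary result.** The documents give no figure that would rank it so.
- **Surgeon and centre choose the approach, and total and subtotal gastrectomy are pooled.** Both are reasonable inferences, but neither is stated.

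**Conclusion.** The point holds in this form: the stated tests, estimator and bias-control measures of a non-randomised comparison include no adjustment for patient factors or baseline utility. Restriction reduces the exposure to patient selection and does not remove it.

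The illustrated bias in INB from baseline utility runs from about EUR 42 (gap 0.05, baseline weight only, lower threshold) to EUR 750 (gap 0.10, persistent, upper threshold). These figures rest on assumed gaps and trapezoid QALYs. The error rates also rest on an SD back-solved from an assumed reading of the EUR 3,000. Bias in cost adds to this by an unknown amount. The utility part alone does not show a large distortion. The case for change is that the primary estimate is open to a known bias and that the baseline measurement needed to reduce it is already collected.

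**What to change.** In Cost-Effectiveness Analysis and Methods for Minimizing Bias, state the following.

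- Within each procedure, the cost and QALY differences, and hence the INB, are estimated with adjustment by regression or by propensity (for example overlap) weighting.
- The adjustment uses a short pre-specified list of patient factors recorded in the eCRF, such as age, sex, ASA, and indication or procedure subtype. Baseline EQ-5D is always in the QALY model.
- Standard errors allow for clustering by centre.
- The tests in Statistical Method are kept as unadjusted, descriptive results.
- The surgeon-experience analysis is kept as secondary, one factor at a time. The Abstract promises to assess the impact of experience, so this analysis should not be dropped. Joint stratification on all three variables should not be relied on at the minimum of 60.

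The list should be fixed before the interim analysis of the primary outcome at 50% inclusion.

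The cost is revised wording, modest analysis work and some loss of precision if the arms overlap poorly. Baseline EQ-5D is already collected. Clinical Data does not list age, sex or indication among the items it names, so their presence in the eCRF should be confirmed.
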